### Participating centres

The three participating centres, including Shengjing Hospital of China Medical University in China, Qilu Hospital of Shandong University in China, and Institut Paoli Calmettes in France, were selected at the workshop of the International Society of Endoscopic Ultrasound (ISEUS). This selection was based on the fact that a few experts are capable of performing EUS-AG over the world, and the number of EUS-BD procedures is relatively higher at these centres. The background characteristics and procedures of this protocol were approved by all the centres involved.

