### Randomisation and interventions

The randomisation list will be generated by an independent statistician using block randomisation with variable block size (four or six) and kept in sealed envelopes without access by the investigators. Once a patient is enrolled by project secretary, the trial coordinator in Endoscopy Center of Shengjing Hospital of China Medical University will open an envelope and publish the final result of randomisation to all trial participants after confirmation, as this is an open-label design.

The equipment used will include a linear array echoendoscope (EG3830UT; Pentax, Tokyo, Japan) in combination with an ultrasound scanner (EUB 6500; Hitachi, Tokyo, Japan). A 19-G needle (EUS N-19-T; Wilson-Cook Medical, Winston-Salem, NC, USA) will be used for puncture, and a 0.035-in. guidewire (Jagwire; Boston Scientific, Natick, MA, USA) will be used for guidance. A cystotome (6 Fr; Wilson-Cook Medical) will be used to dilate the tract and create a large fistula. A fully covered metallic stent (Wilson-Cook Medical/Boston Scientific) or bare metallic stent (Wilson-Cook Medical/Boston Scientific) will be used for biliary drainage.

The former part of the procedure is the same for both EUS-AG and EUS-HGS. First, the echoendoscope will be advanced into the stomach, and the left lateral lobe liver will be scanned. A dilated IH bile duct close to the gastric wall will be selected as the puncture point. Then, to avoid the blood vessels in the puncture path, the local vasculature will be checked using colour Doppler ultrasonography, and a 19-G ultrasound puncture needle will be advanced into the IH duct. Next, bile aspiration and cholangiography will be performed to further clarify the location of the puncture needle and delineate the dilated biliary tree down to the point of obstruction.

In the AG group, a guidewire will be inserted through the puncture needle and guided into the intestine through the ampulla or anastomosis. A temporary fistula between the stomach (or jejunum in patients with total gastrectomy) and the left hepatic duct will be formed by cystectomy. Once the fistula has been dilated, a self-expandable bare metallic stent measuring 6–8 cm will be deployed into the malignant biliary obstruction in an antegrade fashion.

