### Statistical analysis

#### Sample size calculation

The statistical significance level is set at 5%, power of the test is set as 80%, and randomisation ratio is set as 1:1. Based on previous data, the overall success rate of EUS-HGS is 84.5–100% with complication rates of 19.6–27% [5, 17–20]. The overall success and complication rates of EUS-AG are 57–100% and 0–5%, respectively [11, 21, 22]. Using a standard sample size formula, we calculated that 74 patients per group will be needed for a total of 148 patients, after accounting for a 10% dropout rate. A provisional deadline for patient recruitment is set in July 2022; however, in case the target number of patients has not been met, the recruitment period may be extended to reach the number required (2 × 67 patients) to obtain a power of at least 0.8 (80%).

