#### Statistical analysis

The full analysis set (FAS) should be as close as possible to the intention-to-treat set. On the basis of the FAS, patients assigned to the two subgroups, including the HGS and AG groups, would form the per-protocol set. The direct deletion method will be used to treat missing data.

The technical success rate, clinical remission rate, and complication rate will be presented with 95% confidence intervals and compared between the procedures using the chi-square test. Normally distributed continuous variables, such as stent patency, bilirubin level, length of hospital stays, and hospitalisation expenses will be expressed as mean ± standard deviation and will be compared using the *t* test. Concerning the secondary endpoint, Kaplan–Meier methods will be used to compute the survival analyses. The log-rank test and Cox regression analysis will be used to compare the prognosis among patients in the HGS and AG groups. Statistical analyses will be performed using SPSS® Statistics (version 25.0; IBM Corp., Armonk, NY, USA). A two-tailed distribution will be used, and statistical significance will be considered when *P* < 0.05.

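### The planned t tests for expenses, length of stay and bilirubin leave out centre and baseline bilirubin, so the cost comparison in particular may lose power to between-country variation

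*Protocol article*

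**What the plan says.** All references are to the protocol article.

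- **Participating centres:** two hospitals in China and one in France, chosen partly because only "a few experts are capable of performing EUS-AG over the world".
- **Randomisation and interventions:** "The randomisation list will be generated by an independent statistician using block randomisation with variable block size (four or six"). Stratification by centre is not mentioned.
- **Statistical analysis:** technical success, clinical remission and complications are compared by chi-square test. Stent patency, bilirubin level, length of stay and "hospitalisation expenses will be expressed as mean ± standard deviation and will be compared using the" t test. They are introduced as examples of normally distributed variables. Log-rank and Cox regression are named for prognosis, without covariates.
- **Primary endpoints and Data collection:** clinical remission is judged against the patient's own pre-procedural bilirubin, and liver function and biochemistry are tested the day before the operation. The baseline value therefore exists.
- **Secondary endpoints:** stay and expenses are listed. Bilirubin level as a continuous comparison is not.
- **Abstract and Discussion:** the economic results are presented as something that may influence a patient's choice of procedure.

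**The concern.** Hospital expenses in China and France arise in different currencies and price systems, and discharge practice may differ too. A two-sample t test that ignores centre treats these differences as patient-to-patient noise. The wider the gap between countries, the larger the standard error and the less the trial can say about a cost difference between procedures, which is a result the authors intend patients to use.

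Bilirubin has the same problem in another form. A patient's level after drainage is likely to be related to the level before it, and a plain t test discards that information.

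This is more than detail left to a fuller plan, because the article names the test. The covariates that would improve it are already collected.

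**Working it through.** **Inputs from the article.** "The statistical significance level is set at 5%, power of the test is set as 80%, and randomisation ratio is set as 1:1"; tests are two-tailed. The evaluable number is 67 per arm, raised to 74 for dropout: 67 × 1.10 = 73.7, rounded up to 74. The check uses 67 per arm. The article gives no mean, SD or country gap for expenses or stay and no expected recruitment per centre, so there is no figure of the plan's own to reproduce here.

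**Assumed inputs.** Lognormal expenses, within-centre coefficient of variation (CV) 0.5, true arm ratio 1.2, French share f of 10%, 20% or 33%, and a country ratio R in mean expenses after conversion to one currency.

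**Pooled t test.** Set the mean in the cheaper country's reference arm to 1.

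- Pooled mean: m = 1 + f(R − 1)
- Arm difference: 0.2m
- Reference-arm variance: V = 0.25(1 − f + fR²) + f(1 − f)(R − 1)². The first term is within country, the second between countries.
- The other arm has variance 1.2² × V = 1.44V, so SE = √(2.44V/67)
- Power ≈ Φ(0.2m/SE − 1.96)

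Worked case, f = 1/3 and R = 2: m = 1.333, difference 0.267, V = 0.500 + 0.222 = 0.722, SE = √(2.44 × 0.722/67) = 0.162, z = 1.644, power = Φ(−0.316) ≈ 38%.

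| Country ratio R | f = 10% | f = 20% | f = 33% |
|---|---|---|---|
| 1 | 55% | 55% | 55% |
| 1.5 | 52% | 49% | 48% |
| 2 | 43% | 39% | 38% |
| 4 | 21% | 19% | 20% |

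Simulation with blocks of four or six and 134 patients agrees: 55–56% with no gap, about 40% at 2-fold and 19–21% at 4-fold.

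**Centre-adjusted log model.** σ² = ln(1 + 0.5²) = 0.223, so σ = 0.472. The effect is ln 1.2 = 0.182 and SE = 0.472 × √(2/67) = 0.0816. Then z = 2.23 and power = Φ(0.27) ≈ 61%, whatever R is. Simulation gives about 60%. The roughly 5-point advantage at R = 1 comes from the log scale, not from adjusting for centre.

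**A second model, with an additive gap.** Let the country gap be D within-centre SDs. The pooled SD is √(1 + f(1 − f)D²) times the within-centre SD. For the effect that 67 per arm detects with 80% power (0.484 SD), simulated power over the three shares is 72–76% at D = 1 and 37–54% at D = 3, against about 79% with adjustment. Between-country variance is 8–18% of the total at D = 1 and 45–67% at D = 3.

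**Type I error.** In the additive-gap simulations the unadjusted t test rejects a true null in 4.7–5.4% of trials.

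**Bilirubin.** With baseline correlation ρ, ANCOVA multiplies the residual variance by 1 − ρ². Where adjustment would give 80% power, the plain t test gives 76%, 68% and 52% for assumed ρ of 0.3, 0.5 and 0.7.

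**Primary endpoint.** In a simulation of 134 patients in three centres (40/40/20%) with success of about 94% against 77%, chi-square and Cochran–Mantel–Haenszel had power of 0.81 and 0.80 with no centre gap, and 0.80 and 0.81 at a 15-point gap. A 19:11 split in a 30-patient centre with success 15 points lower shifts the overall difference by (19 − 11)/74 × 15 ≈ 1.6 points.

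**The case against.** The strongest reply is that every size above rests on assumed values. With a 1.5-fold gap or less, the t test loses at most about 7 points (55% to 48% at f = 33%). That stands: the loss could be small. For stay, no size is shown at all.

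The wording on normality can be read as applying the t test only where the data are normal, and currency conversion or extra covariates could sit in a fuller plan. That also stands in part, so neither silence is counted as an error here. It does not remove the point that a specific unadjusted test is named for these variables.

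Bilirubin level is not a listed endpoint, and where bilirubin decides an outcome the remission definition already uses the baseline. The bilirubin part is therefore the lesser one.

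Three stronger readings are tempting and not supported:

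- **That country differences swamp expenses and stay.** This needs a gap of about 3 within-centre SDs or more, and the documents give no figure from which to judge it.
- **That centre differences will pass for treatment effects.** Allocation is randomised, there is no bias on average, and the test's error rate already covers chance imbalance between centres.
- **That the primary endpoint is harmed.** The simulation shows no material loss. Nor is every planned comparison an unadjusted test, since Cox regression is also named.

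**Conclusion.** The point holds for the analyses by t test, chiefly hospitalisation expenses. The article fixes an unadjusted comparison pooled over two countries and leaves out centre and baseline bilirubin, both of which will be on record. The consequence is lost precision with a type I error near 5%.

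For expenses, the assumed scenarios put power at about 55% with no country gap, about 40% at 2-fold and about 20% at 4-fold, against about 60% with a centre-adjusted log model. These figures rest on the assumed CV of 0.5, the 20% difference and the 10–33% French share. The actual loss is unknown. It is a modest point about secondary analyses, worth making because the remedy is nearly free.

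**What to change.** Amend the Statistical analysis section as follows:

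1. Convert expenses to one currency at a stated rate and price year.
2. Compare expenses and length of stay with a centre-adjusted model, either linear on the log scale or gamma with a log link, and show results by country as well.
3. Compare log bilirubin by ANCOVA with log pre-procedural bilirubin and centre as covariates.

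The cost is slightly more analysis and estimates expressed as ratios. A log-scale linear model compares geometric means, while a gamma model with a log link compares arithmetic means, which may suit expenses better. No extra data or patients are needed.

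A separate blocked list per centre and a Cochran–Mantel–Haenszel test for the primary composite are optional. Small blocks within each centre make the next allocation easier to guess in an open-label trial, so separate lists are a trade-off rather than a clear gain.

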#### Monitoring

An independent group of statisticians and physicians will constitute the monitoring committee and will perform visit monitoring on a semi-annual basis. None will have direct involvement in the conduct of this study, nor financial, nor professional interests. The monitoring committee will collect information on the status of accumulation, inclusion/exclusion criteria, and serious adverse events and will strive to provide feedback to participating institutions for early resolution if there are any problems. At the end of the trial, a meeting will be hosted by the participating centres and the monitoring committee to evaluate the final data.

#### Publication of results

We plan to publish the results of this study in a peer-reviewed medical journal, should the results be of sufficient scientific interest.

## Discussion

The choice of drainage approach depends on a patient’s individual anatomical structure, underlying disease, and location of biliary stricture. Both HGS and AG are applicable to patients undergoing malignant biliary obstruction with unreachable papillae. Efficiency and safety are important for such patients, because it is difficult for them to tolerate several procedures and postoperative complications. For these reasons, it is important to develop strategies that would permit them to choose EUS-HGS or EUS-AG, weighing both efficiency and safety.

Several studies have reported the efficiency and safety of EUS-HGS and EUS-AG. Artifon et al. compared the safety and efficiency of EUS-HGS and ultrasound-guided choledochoduodenostomy (EUS-CDS) in a randomised controlled trial, and reported that the technical success rate, clinical success rate, and incidence of complications of HGS were 96%, 91%, and 20%, respectively [18]. Uemura et al. systematically searched the literature up to April 8, 2017, and compared the technical success rates, clinical success rates, and incidences of complications of EUS-CDS and EUS-HGS in systematic evaluation and meta-analysis. The technical success rates, clinical success rates, and incidences of complications were 93.7%, 84.5%, and 18.8%, respectively [19]. In a prospective cohort study, Do Hyun et al. found that the success rate of EUS-HGS was 89%, the incidence of complications was 12.5%, and the success rate of EUS-AG was 57%. In their study, no patient in the EUS-AG group experienced postoperative complications [17]. Iwashita et al. reported that the overall success rate and incidence of complications of EUS-AG were 77% and 5%, respectively, by directly adding the number of cases reported in each searched study [23]. Contrary to other previous reports, Ardengh et al. reported that the success rates of EUS-HGS and EUS-AG were 83.3% and 100%, respectively, by reviewing the different EUS-BD approaches in two hospitals [11]. According to most current studies, the success and complication rates of EUS-AG are both lower than those of EUS-HGS. This may be because EUS-AG is more complex and no permanent fistulas or changes of anatomical structure are created [9]. Nevertheless, the stent in EUS-AG is placed through the tumour, and the growth of the tumour is the main cause of stent re-obstruction. Because a perforating fistula is absent, another intervention for postoperative obstruction will be more difficult in EUS-AG than in EUS-HGS [24]. EUS-HGS may result in more pneumoperitoneum and bile leaks because the fistula traverses the peritoneum [12]. Intraperitoneal deployment is also a potential adverse event of EUS-HGS, which can be fatal [25, 26].

To date, all reports of the safety and efficiency of EUS-HGS and EUS-AG were based on observational studies and randomised controlled studies with another technology or evidence-based medicine. Ardengh et al.’s contradictory findings also appeal to the need for a further comparative study of EUS-HGS and EUS-AG. To our knowledge, ours will be the first study to compare these two EUS-BD approaches directly in a multicentre, randomised, controlled trial. The clinical economic indexes will also be compared, as they may also affect the patient’s choice.

There are limitations to the present study design. The internal biliary drainage operation is a palliative treatment for unresectable malignant biliary obstruction. The lifetime of patients included is limited, because death caused by cancer progression is inevitable. Therefore, the long patency of the stent is difficult to evaluate.

## Trial status

The protocol version number is Ver 1.4, which was registered on 15 January 2019 (ChiCTR1900020737). Patient enrolment will begin on 1 August 2020, and completion is expected by 31 August 2022.

## Data Availability

The datasets used and/or analysed during the current study are available from the corresponding author on reasonable request.

## Abbreviations

ERCP: Endoscopic retrograde cholangiopancreatography
EUS-BD: Ultrasound-guided biliary drainage
IH: Intrahepatic
RV: Rendezvous technique
EUS-HGS: Endoscopic ultrasound-guided hepaticogastrostomy
EUS-AG: Endoscopic ultrasound-guided antegrade technique
HGS: Hepaticogastrostomy
AG: Antegrade technique
ChiCTR: Chinese Clinical Trial Registry
CT: Computed tomography
FAS: Full analysis set
EUS-CDS: Endoscopic ultrasound-guided choledochoduodenostomy
